### Data source and privacy

2.9

This RCT is entirely based on routinely collected claims data. The data extracted and used for this trial are provided by the three Swiss health insurers Sanitas, CSS, and Helsana using the physicians' license number ("Zentralregisternummer" i.e. ZSR number). The ZSR number is centrally distributed and provided for all licensed physicians in Switzerland by SASIS/Santésuisse. The information are pseudonymized in the data to ensure confidentiality of records not allowing to identify individual physicians or their patients or the health insurer by the trial investigators. Based on the ZSR numbers, the coordinating data manager from one (Sanitas) of the three health insurers created a unique identifier for each GP. The unique GP identifier allows for the analysis of pseudonymized claims data per physician and per patient, but these identifiers cannot be linked to ZSR numbers by the study investigators or the study staff at any time.

Quarterly prescription feedbacks were prepared by one trial statistician not further involved in the analysis, and printed and packaged by staff not otherwise involved in the trial. Physicians' unique pseudonymous identifiers could be seen in the window of letter envelops containing personalized prescription feedback. The physicians' address was then stuck on the window of the envelope by an independent person not involved in the trial who was in possession of a list of all physician's addresses and the unique pseudonymous identifier. This list was kept on a different password-protected server that could not be accessed by any other person.

The specified study datasets are securely transferred in encrypted format from health insurers to the study server at University Hospital Basel. Study data are stored and processed on infrastructure located within the University Hospital Basel. Data management was conducted in accordance with the procedures used for trial data management by the clinical trial unit. Access to the dataset is strictly limited to the data manager and the statistician of the project.

### Claims database

2.10

Claims data was formatted by data managers of all three health insurers according to a protocol in a standardized fashion that allowed for data import and the identification of the relevant physician population, the generation of the antibiotic prescribing feedbacks and for the generation of the full claims data set for the final analysis. The relevant variables of claims data can be grouped into five categories, physician identifiers and demographics (Table 1 a)), patient identifier and demographics (Table 1 b)), consultation data including the primary outcome data of antibiotic prescribing (Table 1c)), claims consultation data with relevant diagnostic test ordering, prescribing of all medication (pharmacy costing groups) (Table 1 d)), and hospitalization data (Table 1 e)). Due to the size of the data, only data sets 1a) to 1c), were provided by insurers for the intervention phase (generation of personalized prescribing feedback) of the trial. By the nature of claims data (administrative data), we expected very few missing data, hence, no specific procedure to handle missing data is planned.

**Table 1 tbl1:** Description of routinely collected data – basic information of primary care physician and consulations

Variable groups	Description of variables
Table 1a) Physician identifier and demographics	
Physician identifier	Encrypted number (pseudonymized ZSR number)
Canton	Location of the practice (Swiss cantons)
Speciality	General internal medicine, pediatrics or family doctor
Table 1b) patient identifier and demographics	
Patient Identifier	Encrypted number (pseudonymized from health insurerdatabases)
Age category (in 2017)	For years 0–5; 6–10; 11–15; in 5-year categories up to registered maximum age
Majority	Yes/no
Gender	Male, female
Insurance membership Identifier	Pseudonymized codes for the three health insurers
Table 1c) consultation data including the primary outcome data of antibiotic prescribing	
Consultation	Date of consultation, specific Tarmed code(s) and total number of Tarmed code(s)
Table 1d) claims consultation data with relevant diagnostic test ordering, prescribing of all medication (pharmacy costing groups)	
Diagnostic	Date of laboratory analysis, code(s) from the list of laboratory analyses
Pharmacy-Cost groups	Date of the prescription, complete ATC code, total number of prescriptions in ATC group, total costs according to claims in CHF, costs per package
Antibiotics	Date of the prescription, all pharma codes from ATC group J01, complete ATC code (ATC group J01), number of prescribed packages, total costs according to claims in CHF, costs per packages in CHF
Table 1e) Inpatient information	
Hospitalization	Date of hospital admission, date of hospital discharge, DRG code(s)

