### Intervention and control

2.5

The first mailing was sent on December 22, 2017 and was followed by seven additional quarterly mailings, with the last mailing sent in late September 2019 (see the timeline in Fig. 1). With the first mailing, all GPs in the intervention group received (1) an accompanying letter explaining the intervention, assuring the full pseudonymization of feedback data, (2) a personalized feedback of antibiotic prescribing; (3) a response card for physicians wishing to opt-out; and (4) evidence-based guidelines on antibiotic prescribing for respiratory and urinary tract infections (see details below). No information on the study design or comparative study purpose was provided.

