### Outcomes

2.8

The primary outcome is the overall antibiotic use, defined as prescribed antibiotics per 100 patient consultations in the second year of intervention lasting from month 13 to month 24 (long-term intervention effect).

The secondary outcomes are (1) overall antibiotic use defined as prescribed antibiotics per 100 patient consultations from month 1–12 (first year of intervention, shorter-term intervention effect); (2) overall antibiotic use defined as prescribed antibiotics per 100 patient consultations over the entire intervention period from month 1 to month 24, with two repeated measurements, over the first and the second 12 month period of intervention; (3) use of broad-spectrum antibiotics (quinolones and oral cephalosporines) per 100 patient consultations; (4) hospitalizations rates (all-cause and related to infections based on Diagnosis Related Groups (DRG) definition); (5) Antibiotic use (prescribed antibiotics per 100 patient consultations) in five specific age groups, in patients 0–14 years, 15–24 years, 25–54 years, 55–64 years, and ≥65 years; and (6) secondary outcomes (3) to (5) will be evaluated separately over the second and first 12 months (from month 13 to month 24 and 1–12 months).

All cause hospitalization will be defined as any hospitalization (DRG-based) within 30 days after a preceeding GP consulation. Infection-related hospitalization will be defined as any hospitalization within 30 days after a preceeding GP consulation with DRG-codes for community acquired pneumonia, urinary sepsis, or sepsis. Reconsultation will be defined as any consultation within 30 days after a first GP consultation or any emergency consultation in a hospital.

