### Data analysis

2.11

Statistical analysis will be performed by the trial statistician using R (R Core Team 2017 [20]). All analyses will be conducted using the final dataset, which will be available in September 2020 (see also timeline in Fig. 1C) and will follow CONSORT guidelines and intention-to-treat principles [[22], [23], [24]]. A flowchart will describe the inclusion and follow-up of GPs by study arm. Baseline characteristics will be described by study arm with summary statistics such as median and interquartile range or number and percentage; no formal testing between arms will be performed [25]. Outcomes will be described by arm using summary statistics.

The primary outcome, the proportion of individuals with an antibiotic prescription in the second year of the intervention, will be assessed by ANCOVA modeling, with the outcome as a response, intervention (yes/no) as a factor of interest, and baseline year antibiotic prescription rate as a covariate (the baseline year is January–December 2017). Other baseline covariates of interest include comorbidities (based on pharmacy cost groups) patients' age, annual patient volume (total number of consultations per GP), and seasonality. For the primary outcome analysis, the coefficient estimates and their 95% CI will be reported. Secondary outcomes will be evaluated in the same way.

Effects for the period month 1 to month 24 will be modeled using a linear mixed model including the intervention (yes/no), time (baseline, first year, second year), an interaction term for the intervention with time, and by treating physician as random effects. Mean percentage changes from baseline will be derived for the intervention and control groups. Other baseline covariates of interest will be included as for the primary analysis.

The rates of hospitalizations and reconsultations will be modeled using logistic regressions including the intervention as a factor of interest and other relevant covariates. Hospitalization rates in the intervention and control group, with exact 95% CIs will be reported, and odds ratios for the intervention arm vs. control will be derived from the coefficients estimated for the logistic regression model.

The analysis in specific age groups will be similar to the primary analysis over the respective periods and stratified by age groups i) 0–14 years, ii) 15–24 years, iii) 25–54 years, iv) 55–64 years, and v) 65 years and over.

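### The age bands listed in Table 1b do not allow the five age groups of secondary outcome (5) to be formed as defined

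*Protocol article*

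**What the plan says.** Section 2.10 (Claims database), Table 1b, describes the age variable in the insurers' data. It is labelled "Age category (in 2017") and banded "For years 0–5; 6–10; 11–15; in 5-year categories up to registered maximum age". The only other age item is a yes/no flag for majority. The text of 2.10 says the standardised format served both the feedback and the full data set for the final analysis.

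Section 2.8 (Outcomes), secondary outcome (5), sets antibiotic use "in patients 0–14 years, 15–24 years, 25–54 years, 55–64 years, and ≥65 years". Section 2.11 (Data analysis) repeats the same groups: "stratified by age groups i) 0–14 years, ii) 15–24 years, iii) 25–54 years, iv) 55–64 years, and v) 65 years and over". Item (6) of 2.8 adds that this outcome "will be evaluated separately over the second and first 12 months".

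On timing, section 2.5 states "The first mailing was sent on December 22, 2017", and section 2.11 states that "the baseline year is January–December 2017". Months 1–12 are therefore about calendar 2018 and months 13–24 about calendar 2019.

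**The concern.** Groups can be built from banded data only if every group boundary is also a band boundary. Here the bands end in 5 (at 15, and by continuation at 25, 55 and 65), while the analysis groups end in 4 (14, 24, 54, 64). The two specifications conflict, and nothing in the article says how a straddling band is to be allocated.

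At stake is a named secondary outcome. Unless a rule is fixed in advance, the allocation would be chosen once the data are available, and the published group labels would not match the patients in them. Section 3 presents patient-level data as the remedy for the pilot trial's limited subgroup analyses, so the age field should support the groups that were prespecified.

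**Working it through.** No sample size or power figure is involved; the check is an enumeration.

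**Inputs.** Bands from Table 1b: 0–5, 6–10 and 11–15 as printed. The later bands are not printed. The contiguous continuation in 5-year steps is 16–20, 21–25, …, 51–55, 56–60, 61–65, 66–70, and so on. Group cuts from 2.8 and 2.11: 14|15, 24|25, 54|55 and 64|65.

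**Rule.** A cut between c−1 and c splits a band running from a to b when a < c ≤ b.

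| Cut | Band in 2017 | Test | Same band in 2018 | Same band in 2019 |
|---|---|---|---|---|
| 14\|15 | 11–15 (printed) | 11 < 15 ≤ 15: split | 12–16: split | 13–17: split |
| 24\|25 | 21–25 (continued) | 21 < 25 ≤ 25: split | 22–26: split | 23–27: split |
| 54\|55 | 51–55 (continued) | 51 < 55 ≤ 55: split | 52–56: split | 53–57: split |
| 64\|65 | 61–65 (continued) | 61 < 65 ≤ 65: split | 62–66: split | 63–67: split |

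All four cuts are split, and ageing the bands forward by one or two years rescues none of them. The majority flag does not help. The article does not give its age, but a flag for adulthood would not be expected to separate 14 from 15, and it cannot serve the three higher cuts.

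**Nearest groups that can be formed.** Each straddling band has four single-year ages below the cut and one above, so the closest allocation puts the whole band in the lower group. This gives 0–15, 16–25, 26–55, 56–65 and ≥66. Counting single-year ages in 2017 that lie outside the stated label:

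- 0–15: 1 of 16 (age 15)
- 16–25: 1 of 10 (age 25)
- 26–55: 1 of 30 (age 55)
- 56–65: 1 of 10 (age 65)
- ≥66: none, although age 65 is missing from the group

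These are counts of ages, not of patients; the article gives no age distribution from which to weight them.

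**Effect of fixing age in 2017.** This matters only if the groups are meant as age at consultation. Under that reading, patients aged 14, 24, 54 or 64 in 2017 belong to another stated group by 2018, and those aged 13–14, 23–24, 53–54 or 63–64 by 2019. The 16–25 band group would be 18–27 in 2019, with 3 of 10 ages (25, 26, 27) outside 15–24. One of those three years comes from the band edge and two from the fixed year. Under any reading, children born in 2018–2019 have no 2017 category.

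**The case against.** The strongest reply is that Table 1 is a summary of basic information and that the insurers worked to a data-format protocol that is not shown, where a finer age field may exist. Only the band 11–15 is printed in full among those that matter; the other three conflicts rest on a natural continuation. There is also an unstated reading that would remove the problem. If the 2017 category is 2017 minus birth year, age at 31 December 2016 is one year lower, the bands become 10–14, 15–19, 20–24 and so on, and all four cuts align. These points limit how firmly one can say the outcome cannot be computed. They do not remove the conflict between Table 1b and sections 2.8 and 2.11, because the article states neither a finer field nor that definition.

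It is also fair to say that grouping by age in the baseline year is legitimate and keeps patients in one group across both follow-up years. That stands: the fixed year alone does not prevent groups from being formed. What remains is that the reference age is not stated and that later births are unclassified.

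A reader might infer more than the documents support:

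- **That the primary outcome is compromised.** It is overall antibiotic use per 100 consultations and needs no age groups.
- **That the arms are compared unfairly.** The banding is the same in both arms, so a comparison within any band-based group remains randomised.
- **That patients in every group are mislabelled.** Everyone aged 66 or over in 2017 is truly 65 or over.
- **That the age effects seen in the pilot would be lost.** Section 1 reports those for ages 6–18, which is not one of the five groups, and for younger adults without an age range. Nothing shows that a one-year boundary shift would hide them.

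**Conclusion.** The point holds as an internal conflict: the age variable listed in Table 1b cannot produce the five groups fixed in 2.8 and 2.11. One cut of four is contradicted by a printed band. The other three are contradicted on the assumption that 5-year bands continue from 16. The nearest feasible grouping moves each boundary by one year, so one single-year age is misplaced at each of the four cuts. The harm is inexact labels and some blurring of the age-specific estimates. The undefined reference age and the missing category for children born in 2018–2019 are a smaller, separate gap.

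Severity is moderate and confined to secondary outcome (5). The conclusion assumes that Table 1b describes the age field available for the final analysis, as the text of 2.10 indicates.

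**What to change.** Choose one of two routes and make 2.8, 2.10 and 2.11 agree.

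(a) Obtain year of birth or single-year age in the final extract, form the five stated groups from it, and state the reference date. This costs one additional field from the insurers, and that field is slightly more sensitive in pseudonymised data.

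(b) Keep the supplied field and redefine the groups in 2.8 and 2.11 as age in 2017: 0–15, 16–25, 26–55, 56–65 and 66 or over. Assign children born after 2017 to the youngest group. This is a change of wording plus one assignment rule. The groups should not be updated yearly, because a band fixed in 2017 does not allow it: by 2019 the band 11–15 covers ages 13–17 and straddles the new 15|16 edge as well. The cost is that the labels no longer match the age groups originally stated.

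If the full data specification already holds a finer age field, correct Table 1b to show it and state the reference date for age; no new data are then needed.

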### Data analysis

2.11

Statistical analysis will be performed by the trial statistician using R (R Core Team 2017 [20]). All analyses will be conducted using the final dataset, which will be available in September 2020 (see also timeline in Fig. 1C) and will follow CONSORT guidelines and intention-to-treat principles [[22], [23], [24]]. A flowchart will describe the inclusion and follow-up of GPs by study arm. Baseline characteristics will be described by study arm with summary statistics such as median and interquartile range or number and percentage; no formal testing between arms will be performed [25]. Outcomes will be described by arm using summary statistics.

The primary outcome, the proportion of individuals with an antibiotic prescription in the second year of the intervention, will be assessed by ANCOVA modeling, with the outcome as a response, intervention (yes/no) as a factor of interest, and baseline year antibiotic prescription rate as a covariate (the baseline year is January–December 2017). Other baseline covariates of interest include comorbidities (based on pharmacy cost groups) patients' age, annual patient volume (total number of consultations per GP), and seasonality. For the primary outcome analysis, the coefficient estimates and their 95% CI will be reported. Secondary outcomes will be evaluated in the same way.

Effects for the period month 1 to month 24 will be modeled using a linear mixed model including the intervention (yes/no), time (baseline, first year, second year), an interaction term for the intervention with time, and by treating physician as random effects. Mean percentage changes from baseline will be derived for the intervention and control groups. Other baseline covariates of interest will be included as for the primary analysis.

The rates of hospitalizations and reconsultations will be modeled using logistic regressions including the intervention as a factor of interest and other relevant covariates. Hospitalization rates in the intervention and control group, with exact 95% CIs will be reported, and odds ratios for the intervention arm vs. control will be derived from the coefficients estimated for the logistic regression model.

The analysis in specific age groups will be similar to the primary analysis over the respective periods and stratified by age groups i) 0–14 years, ii) 15–24 years, iii) 25–54 years, iv) 55–64 years, and v) 65 years and over.

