**Methods and analysis:**

1713 GPs randomized to the intervention group received once evidence-based treatment guidelines at the beginning, including region-specific antibiotic resistance information from the community and personalized feedback of their antibiotic prescribing, followed by quarterly personalized prescription feedback for two years. The first and the last mailings were sent out in December 2017 and September 2019, respectively. The 1713 GPs randomized to the control group were not notified about the study and they received no guidelines and no prescription feedback. The personalized prescription feedbacks and the analyses of the primary and secondary outcomes are entirely based on pseudonymized patient-level data from routinely collected health insurance data. The primary outcome is prescribed antibiotics per 100 patient consultations during the second year of intervention. The secondary outcomes include antibiotic use during the entire two-year trial period, use of broad-spectrum antibiotics, hospitalization rates (all-cause and infection-related), and antibiotic use in different age groups. If the feedback intervention proves to be efficacious, the intervention could be continued systemwide.

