### Study population, sample size, and power analysis

2.3

The data provided by the three health insurers Sanitas, CSS, and Helsana, comprise information on a total of 8422 primary care physicians in Switzerland. These primary care physicians treated at least one patient covered by one of the three health insurances. Due to the usual administrative processing delay of claims data of 6 months by health insurers, the definitive sample size calculation had to be based on claims data from January to December 2016. In this pre-randomization claims data set, we identified 3646 eligible GPs corresponding to the inclusion criteria, as mentioned above. A random sample of 220 physicians from the Basel area was left aside for a different interventional trial. The remaining study population of 3426 physicians were randomized to the intervention or control groups, with 1713 physicians in each arm.

We conducted a power analysis that was based on a trial simulation from 50 bootstrap samples. These bootstrap samples were extracted from the pool of physicians from the database of the year 2016, which was used to select and randomize GPs. The clinically relevant effect that the study aims to detect is, on average 5% expected reduction in prescription rates. Therefore, we simulated a trial for each bootstrap sample and we applied the effect which we expected to observe in the treatment arm. To also account for any variability, we simulated effects from distribution of potential effects, which were "centered" around 5%, for every physician. The standard deviation of the prescription rate in the target population was evaluated based on the data from the year 2016, which was 0.059 on the raw scale and 0.438 on the log scale. Also, we scaled the distribution to account for the expected proportion of non-responders of 15%. For each sample, we then tested the difference using a Mann Whitney *U* test (Wilcoxon rank-sum). Hence, we evaluated the power for each bootstrap sample, and derived medians and confidence intervals from the empirical distribution, which gave an estimated median power of 0.93 (95% CI: 0.90 to 0.96).

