### Personalized antibiotic prescribing feedback

2.6

The personalized antibiotic prescription feedback contained 1) the personal yearly prescription rate (antibiotic prescriptions per 100 consultations) compared with the prescription rates of the peer-physicians, 2) the personal monthly prescription rates for the three months for the same period of the preceding year and its comparison with peer-physicians (the first feedback mailing was based on antibiotic prescription rates between April 2016 to March 2017), 3) the personal yearly prescription rate (antibiotic prescriptions per 100 consultations) stratified by type of antibiotics and compared with the prescription rates of peer-physicians, and 4) a call to action information in a blue box, which varied with each mailing (see example Fig. 2). Personalized antibiotic prescription feedback was provided every three months in the form of a postal mailing and was continuously updated with the most recent complete health insurance data. As there is a six months delay in the health insurance billing records processing and the time needed to prepare the feedbacks, the yearly prescription feedbacks were based on the data from the period of 9 month prior to each sent mailing. All information material and guidelines were also made available to physicians on a password-protected trial website.

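### Section 2.11 runs the primary ANCOVA on a proportion of individuals, although the primary outcome is defined as prescriptions per 100 consultations

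*Protocol article*

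**What the plan says.** The abstract states: "The primary outcome is prescribed antibiotics per 100 patient consultations during the second year of intervention". Section 2.8 (Outcomes) gives the formal definition: "The primary outcome is the overall antibiotic use, defined as prescribed antibiotics per 100 patient consultations in the second year of intervention", with the window set as months 13 to 24.

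Section 2.11 (Data analysis) then introduces the primary model with a different quantity: "The primary outcome, the proportion of individuals with an antibiotic prescription in the second year of the intervention". That is the response of the ANCOVA. The same sentence adjusts for "baseline year antibiotic prescription rate as a covariate (the baseline year is January–December 2017").

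Two other sections bear on which quantity is meant. Section 2.6 describes the feedback metric as "the personal yearly prescription rate (antibiotic prescriptions per 100 consultations) compared with the prescription rates of the peer-physicians". Section 2.3 bases the power calculation on "on average 5% expected reduction in prescription rates", with a standard deviation of the prescription rate "which was 0.059 on the raw scale and 0.438 on the log scale"; it gives no denominator for that rate.

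**The concern.** A primary outcome should be one quantity wherever it appears, and above all in the sentence that specifies its test. Here the defining section counts prescriptions over consultations, while the analysis section counts people with a prescription over people. An analyst who followed 2.11 to the letter would test a response that 2.8 does not declare.

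The trial itself expects movement in the features that separate the two measures. Section 2.1 lists reconsultation as a possible unintended effect, and the Discussion names repeated prescribing to the same patient as something the patient-level data will show.

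The wording also carries over. Section 2.11 says that secondary outcomes will be handled in the same way and that the age-group analyses will resemble the primary one, whereas 2.8 defines antibiotic use in the age groups per 100 consultations.

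**Working it through.** **1. The two definitions side by side**

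| | Abstract and 2.8 | 2.11 |
|---|---|---|
| Numerator | Antibiotic prescriptions, repeats counted | Persons with a prescription, each counted once |
| Denominator | Consultations | Persons |
| Window | Second year (months 13–24) | Second year |
| Baseline covariate | – | 2017 prescription rate (per 100 consultations in 2.6) |

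The window agrees and the model is not in dispute. Numerator and denominator conflict. The measures coincide only if every patient has one consultation with at most one prescription.

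**2. How they can diverge**

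- *Consultations change, prescriptions do not.* With prescriptions fixed, a 5% fall in the per-consultation rate needs consultations to rise by 1/0.95 − 1 = 5.3%. If these are extra visits by the same patients, the proportion of individuals treated does not move.
- *Repeat prescriptions change, patients treated do not.* If all of a 5% fall in prescriptions comes from second and later courses, the per-consultation rate falls by 5% and the proportion by 0%.

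**3. The plan's power figure**

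Inputs from 2.3: 1713 GPs per arm, a 5% average reduction, log-scale SD 0.438. Two-sided alpha of 0.05 is assumed, as the article does not state it.

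- Difference on the log scale: −ln(0.95) = 0.0513
- z = (0.0513 / 0.438) × √(1713/2) − 1.96 = 3.43 − 1.96 = 1.47
- Power = 0.929. With the Mann–Whitney efficiency factor 3/π it is 0.918. The stated value is 0.93 (0.90 to 0.96).

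The figure reproduces if 5% is the average over all GPs. If the 15% non-responders dilute the 5%, the z formula gives 0.83; the article does not settle which is meant, and this point does not depend on it. The match does not identify the denominator either, because a log-scale SD carries no unit.

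**4. Does the switch of definition cost power?**

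Illustrative assumptions, not in the documents: lognormal rates across GPs, Poisson prescribing, and a fixed k of 2, 4 or 6 consultations per patient-year.

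- Implied mean rate: 0.059 / √(exp(0.438²) − 1) = 0.059 / 0.460 = 0.128 per consultation
- Proportion with at least one prescription: p = 1 − exp(−0.128k)

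| k | p | p after a 5% rate cut | Relative fall |
|---|---|---|---|
| 2 | 22.6% | 21.6% | 4.4% |
| 4 | 40.1% | 38.6% | 3.9% |
| 6 | 53.7% | 51.9% | 3.4% |

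The relative effect is smaller on the proportion, but the spread between GPs shrinks too. For fixed k, p is an increasing function of the rate, so the ranks of the GPs are unchanged and the Mann–Whitney test used in 2.3 gives the same result on either scale. Simulation with 1713 per arm, ignoring sampling error within a GP, confirmed it: power was the same on both scales (0.907 in one simulation, 0.898 in another). The standardised mean difference was 0.109 to 0.110 on the rate (directly, 0.05 × 0.128 / 0.059 = 0.109) and 0.112 to 0.116 on the proportion. This model shows no loss of ability to detect the effect.

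**The case against.** The strongest reply is that the document already shows which definition governs. Section 2.8 is the only place that formally defines outcomes, the abstract agrees, and the feedback letters use the same metric. In 2.11 the baseline covariate is a prescription rate, and the antibiotic-use secondary outcomes, said to be analysed in the same way, are defined per 100 consultations. The phrase in 2.11 looks like a slip. The public definition in 2.8, the blinded statistician of 2.4 and an analysis plan that is not shown all limit the scope for choosing an endpoint after seeing results.

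Most of this stands, and it rules out three stronger readings that a reader might infer:

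- *That the trial has two primary endpoints of equal standing.* It does not: 2.8 defines the outcome and 2.11 misdescribes it.
- *That following 2.11 would cost power because the effect shrinks by 12 to 32%.* The relative falls of 4.4% to 3.4% are correct under their assumptions, but they only show that a percentage means something different on another scale. Detectability is not reduced in that model.
- *That the quantity in 2.11 was certainly never powered.* Section 2.3 speaks of a prescription rate without a denominator. Per consultation is the most natural reading, given 2.6, but it is an inference.

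What the reply does not remove is the contradiction itself. The document positively states two different quantities as the primary outcome, and an analysis plan that picks one would not make this text consistent.

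**Conclusion.** The point holds as a contradiction in current text, confined to one phrase in 2.11. Taken literally, that phrase makes the confirmatory ANCOVA test a response that differs in numerator and denominator from the primary outcome in 2.8 and the abstract, and that does not match its own baseline covariate as 2.6 expresses the prescription rate.

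Its size is qualitative. The two measures can give different answers if reconsultations or repeat prescribing change, and the documents do not give the consultations per patient that would be needed to say by how much. The contradiction rests on the text alone; the 5.3% example assumes unchanged prescriptions and extra visits by the same patients. No change in sample size follows.

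**What to change.** In 2.11, replace the phrase about the proportion of individuals with the 2.8 definition: antibiotics prescribed per 100 patient consultations in months 13 to 24. State that the 2017 baseline covariate is computed on that same definition. Make the same check in the analysis plan, if one exists.

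The cost is one sentence, with no new data and no recalculation. It should be made before the final dataset, due in September 2020, is analysed, so that the choice of response is visibly independent of the results.
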